## Abstract

**Background:**

Motor and non-motor impairments affect quality of life in individuals with Parkinson’s disease. Our preliminary research indicates that forced exercise cycling, a mode of exercise in which a participant’s voluntary rate of exercise is augmented on a stationary cycle, results in global improvements in the cardinal symptoms of Parkinson’s disease. The objective of the *Cyc*lical *L*ower Extremity *E*xercise (CYCLE) trial for Parkinson’s disease is to determine the effects of forced exercise cycling on motor and non-motor performance when compared to voluntary rate cycling and a non-exercise control group. Additionally, we plan to identify any associated changes in neural activity determined by functional magnetic resonance imaging.

**Methods/Design:**

A total of 100 individuals with mild to moderate idiopathic Parkinson’s disease will participate in a single-center, parallel-group, rater-blind study. Participants will be randomized 2:2:1 into a forced exercise, voluntary exercise, or no-exercise control group, respectively. Both exercise groups will cycle 3 times per week for 8 weeks at identical aerobic intensities for 40 minutes, but participants in the forced exercise group will cycle 30% faster than their voluntary rate by means of an augmented motorized bicycle. Neuroimaging, clinical, and biomechanical assessments of motor and non-motor performance will be made at baseline both ‘on’ and ‘off’ medication, after four weeks of exercise (midpoint), end of treatment, 4 weeks after end of treatment, and 8 weeks after end of treatment.

**Discussion:**

CYCLE trial will play a critical role in determining the effectiveness of two different types of aerobic exercise, forced and voluntary, on motor and non-motor performance in individuals with Parkinson’s disease. Additionally, the coupling of clinical, biomechanical, and neuroimaging outcomes has the potential to provide insight into mechanisms underlying change in function as a result of exercise.

**Trial registration:**

Clinicaltrials.gov registration number NCT01636297.

## Background

Parkinson’s disease (PD) is a chronic, progressive neurological disorder that affects an estimated 4 million individuals worldwide [1]. Individuals diagnosed with PD typically experience progressive deficits in motor and non-motor functions which contribute to diminished quality of life, cognitive impairments, fatigue, mood disorders, and anxiety [2-5]. Unfortunately, there is no treatment that can modify the disease process itself. Current therapies include symptom management through medical and surgical interventions; however, these treatments are expensive and can cause adverse side effects. Therefore, the development of a low-cost, non-invasive treatment that can improve symptoms of PD and improve quality of life would be valuable.

It has been well-established that exercise in healthy adults plays a role in decreasing the incidence of cardiovascular, metabolic, and musculoskeletal conditions, as well as preserving cognitive function and preventing dementia and depression [6]. The concept of ‘exercise is medicine’ for PD, is supported by evidence that regular exercise may delay the onset of PD symptoms [7], and can improve motor scores, balance, and quality of gait in those with the disease [8]. Nevertheless, there is still much debate over what type of exercise should be prescribed. A recent Cochrane Review notes that due to small sample sizes, methodological flaws, and a wide range of exercise interventions, there is insufficient evidence to recommend one mode of exercise over another [9].

Aerobic exercise has been shown to reduce inflammation, suppress oxidative stress, and stabilize calcium homeostasis, which all promote brain health [10]. Looking specifically at the role of aerobic exercise in neurological conditions, it may induce neuroplastic changes in the central nervous system (CNS) through the release of neurotrophic factors, which are capable of signaling neurons to survive, differentiate, and grow [11]. Animal models of PD support the importance of aerobic exercise in the release of neurotransmitters and neurotrophic factors, specifically brain derived neurotrophic factor and glial cell derived neurotrophic factor, which have been associated with positively impacting cognition and motor function in animal models of PD [12-15].

Previous studies suggests that exercise interventions must be intense and continuous to elicit benefits on PD symptoms [6,16]. However, individuals with PD typically experience varying levels of rigidity and bradykinesia, which may limit their ability to complete continuous, high-intensity exercise [17-19]. To address these issues, a novel mode of aerobic exercise termed forced exercise (FE) was developed to aid individuals with neurological deficits to achieve and maintain a high cadence pedaling rate. Initially, the FE paradigm was implemented using a tandem stationary cycle where the trainer on the front of the tandem bicycle pedaled between 80-90 rpms, and the individual with PD on the back of the bike was forced to pedal at the same rate due to the pedals on a tandem bike being mechanically linked by the bike chain [20,21]. In a preliminary study completed by [name] and colleagues, motor outcomes were examined after individuals with PD completed 8 weeks of cycling using either the FE approach or voluntary exercise (VE), where individuals cycled on a stationary bike at a self-selected cadence [20,21]. The Unified Parkinson’s Disease Rating Scale (UPDRS) [22] motor subscale score for individuals randomized into the FE group improved 41% for rigidity, 38% for tremor, and 28% for bradykinesia. Additionally, biomechanical analysis of grasping force and torque indicated that FE, but not VE, resulted in an improvement in the coordination and control of grip and load forces during the performance of a bimanual object manipulation task [20,21]. Functional connectivity magnetic resonance imaging (fcMRI) was conducted during the following conditions: 1) on PD medication, 2) off PD medication, and 3) off medication after a single bout of FE. Results demonstrated that FE and PD medication produce similar brain connectivity responses, and likely share similar underlying mechanisms [23]. An improvement in upper extremity motor control processes following a lower extremity exercise intervention coupled with the change in fcMRI indicate that FE is altering brain structure and potentially function in some manner. However, the specific mechanism and identification of the phenotype of PD patients that could benefit from FE is unknown.

Not all studies examining high intensity exercise with PD have had such promising results. In a 2013 study, Qutubuddin and colleagues randomized 23 individuals with PD into a FE and no-exercise control group [24]. After 16 FE sessions, they found no difference between groups in quality of life or motor outcomes, including the UPDRS motor assessment [24]. A significant limitation of their study was that they did not use an active FE intervention. Rather, they used a cycle that could be programmed to move the pedals at a selected speed, however, the participants did not have to actively contribute to the pedaling action. Hence, it was passive high-rate exercise as opposed to FE as we have previously published which requires active participation of the patient. Additionally, participant heart rate (HR), cadence, and power were not reported in the results; therefore, it is not possible to know how much the participants were contributing or if they were experienced an elevated HR that was close to an aerobic zone. Shulman, et al. reported that low-intensity treadmill training produced changes in a 50-ft fast pace ambulation test and 6 minute walk times that were not seen in high-intensity treadmill training, and neither group displayed changes in UPDRS scores [25]. Notably, the low-intensity group received 50 minutes of treadmill training, while the high-intensity group received only 30 minutes; therefore, it is possible that time was an important factor in gait changes.

The *Cyc*lical *L*ower Extremity *E*xercise for Parkinson’s (CYCLE) Trial is designed to test the hypothesis that FE and VE, while both aerobic, produce different clinical outcomes as a result of differential effects on the CNS. Specifically, the aims of the CYCLE trial are: 1) To determine the effects of FE and VE on motor function in individuals with PD; 2) To determine the effects of FE and VE on non-motor function in individuals with PD; and 3) To determine the pattern of magnetic resonance imaging (MRI) activation associated with FE and VE. It is hypothesized that FE will elicit significantly greater improvements in clinical and biomechanical measures of motor and non-motor performance when compared to voluntary and no-exercise control groups. Further, it is hypothesized that FE will elicit increased cerebral blood flow and cortical and subcortical activation following exercise, while voluntary and no-exercise groups will result in no change in the pattern or extent of activation as seen on neuroimaging.

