## Methods and design

### Study design

This single center, prospective, rater-blind, three arm clinical trial will investigate the efficacy of a FE paradigm on motor and non-motor symptoms in individuals with PD. A total of 100 individuals with mild to moderate idiopathic PD will be enrolled. CYCLE Trial protocol is approved by the Cleveland Clinic Institutional Review Board and all participants will sign an informed consent prior to beginning the study. Written informed consent was obtained for any photographs that have been taken for publication. A schematic overview of the enrollment, testing, and intervention is shown in Figure 1.

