### Power analysis

For Aim 1, the UPDRS motor score will be the primary outcome. Our power analysis was calculated based on UPDRS motor data from our previous project comparing FE and VE interventions on UPDRS ratings. We observed a mean (95% confidence interval (CI)) reduction of -5.3 (-18.0, 7.4) in the FE group and 0.4 (-15.3, 16.1) in the VE group from baseline to end of treatment (EOT) at 8 weeks. This corresponds to a difference (improvement, reduction) in means (95% CI) of -4.9 (-20.6, 10.8), standard deviation (SD) of difference = 8.0, P = 0.004. Assuming similar variability for the current proposal, with N = 40 subjects per exercise group, we will be able to detect differences of 5.0 or more between groups on UPDRS with 90% power at the 0.05 significance level, adjusting for 3 group comparisons at each of EOT evaluations. No published data exists for outcomes in Aim 2 or 3 with respect to exercise and PD. In general, with 40 subjects per exercise group, power will be 99 percent to detect differences of 1.2 SDs or more between the groups. For Aims 1-2, comparisons at particular time points power is 90% to detect differences of 1.3 SD, applying a Bonferroni correction for analyzing time points (2 post-intervention times) individually. All calculations assume Tukey adjustment for comparing the 3 groups.

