### Randomization

Participants will be randomized 2:2:1 into FE, VE, or no-exercise control group. The uneven allocation of subjects was selected due to the promising results of the preliminary data by [name], et al. indicating there is a benefit to cardiovascular exercise that would not been seen in a control group [20,21]. Enrollment will total 18 weeks: two weeks allotted for baseline evaluations, 8 weeks of exercise intervention or control period, and 8 weeks for a follow up period in which the participant is instructed to return to their baseline level of physical activity.

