### Data analysis

Participants in all three groups will be compared descriptively on potentially confounding baseline variables (i.e., age, disease severity, and levodopa equivalent daily dose (LEDD)) to assess the extent of any imbalance across groups. Baseline variables in which there appears to be a clinically important baseline difference, or in which the standardized difference (absolute value of difference in means divided by pooled SD) between any 2 groups is greater than 10% will be included as covariates. P-values from these baseline variable comparisons will not be used to determine the need for covariate adjustment, as that criterion can be misleading.

The FE, VE, and the no-exercise control groups will be compared on each outcome of interest (motor, non-motor) using repeated measures analysis of covariance. For motor and non-motor outcomes, groups will be compared on outcomes at the mid-treatment, EOT, EOT + 4 weeks, and EOT + 8 weeks adjusting for the baseline (on and off medication) period as a covariate. The effects of group, time, and the group-by-time interaction will be assessed for each outcome. In the case of a significant interaction, the groups will be compared at each time point. Tukey’s correction for multiple comparisons will be used. Data will be transformed as needed to meet model assumptions. In addition to p-values, the estimated treatment effect and its 95% CI will be of interest as these data will aid in formulating exercise recommendations and potential benefits. For each hypothesis, significance level will be set at 0.05. Each participant’s change in fitness based on change in peak VO_2_ from CPX testing will be used as a covariate. This will remove the effect of possible differences in improvement in fitness level across the groups from confounding the results. Correlation between LEDD and the time spent within target HR zone during training, amount of work performed, and change in primary outcome variables in motor and non-motor outcomes will be assessed. If the LEDD is significantly correlated with these outcomes, it will be included as a covariate in the related analysis.

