### MRI data

Functional imaging data collected during the motor tasks will be retrospectively motion corrected with a slice-based second-order motion model [45,46] in parallel with physiologic noise regression [47], spatially filtered [48] and analyzed for task-related activation using a least-squares fit of the voxel-level BOLD signal to a reference function generated from the task design [49]. The result will be a whole brain map of Student’s t-values reflecting the response of each voxel for each task. A paired *t*-test of the total volume of activation above a t-value of 3.5 (p < 0.001, uncorrected) in the supplemental motor area will be calculated in all subjects. Correlation will be calculated between the change in activation volume of the supplemental motor area and subcortical structures of interest (globus pallidus, putamen, and thalamus) for each subject and the corresponding biomechanical measures during a finger tapping task during the scan and UPDRS rating.

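### Aim 3 predicts no change in activation in the voluntary-exercise and control arms, but the only activation test named is a paired t-test with no group term, which can neither show no change nor compare the arms

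*Protocol article*

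**What the plan says.** All references are to the protocol article.

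- **Background.** The motor and non-motor hypotheses are comparative: FE is expected to improve more than the other two groups. The imaging hypothesis has a different form. FE is expected to raise cerebral blood flow (CBF) and activation, whereas "voluntary and no-exercise groups will result in no change in the pattern or extent of activation as seen on neuroimaging". The same section attributes the expected clinical differences between FE and VE to differing effects on the central nervous system.
- **MRI data.** The activation test is a paired t-test: the "total volume of activation above a t-value of 3.5 (p < 0.001, uncorrected) in the supplemental motor area will be calculated in all subjects". Correlations with finger-tapping and UPDRS measures follow. No group factor appears.
- **Data analysis.** The three-group repeated measures ANCOVA is written for motor and non-motor outcomes; imaging is not named. The section adds: "For each hypothesis, significance level will be set at 0.05".
- **Power analysis.** For imaging, "No published data exists for outcomes in Aim 2 or 3 with respect to exercise and PD". The general statement is that "with 40 subjects per exercise group, power will be 99 percent to detect differences of 1.2 SDs or more between the groups", with Tukey adjustment for three groups. This is a between-group statement.
- **Study design and Randomization.** "A total of 100 individuals with mild to moderate idiopathic PD will be enrolled", and "Participants will be randomized 2:2:1 into FE, VE, or no-exercise control group", which gives 40 FE, 40 VE and 20 control.

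**The concern.** A test of difference can give evidence that activation changed. It cannot give evidence that it did not, because a non-significant result may equally reflect a small arm or a noisy measure. The imaging hypothesis nevertheless has an absence of change as one of its two halves, and the named test does not compare arms.

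At stake is the mechanistic conclusion that FE alters brain activation and VE or no exercise does not. If FE is significant within its arm and another arm is not, that pattern matches the hypothesis as worded, yet no test has shown that the arms differ. The 2:2:1 allocation adds to the problem for the control comparison: an arm half the size of FE is more likely to be non-significant even when its true change is the same.

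**Working it through.** **1. The plan's own figure.** The one power statement that reaches Aim 3 is 99% for a between-group difference of 1.2 SD. The Tukey critical value for 3 groups and 97 df is q/√2 = 2.380. The noncentrality is 1.2/√(1/n₁ + 1/n₂).

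- 40 v 40: noncentrality 5.37, power 99.8%.
- 40 v 20: noncentrality 4.38, power 97.6%.

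The stated figure is reproduced for the exercise arms. It concerns a contrast between arms and says nothing about absence of change within an arm.

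**2. What the named paired test can deliver.** The text allows two readings.

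- *Pooled over all participants.* The result is one average change over 100 people. Nothing is learned about FE, VE or control separately, so the hypothesis is not tested.
- *Run within each arm.* FE can be supported by a significant result. For VE and control, the most the test can yield in favour of the hypothesis is a non-significant one.

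**3. How often the arm-wise test would miss a real change (illustration).** Assumptions: paired t-test within each arm, two-sided 0.05 (the article does not state sidedness), no scan loss, and a true mean change d in units of the SD of within-person change. The article gives no value for d, so a range is shown. Power = P(T > t₀.₉₇₅,ₙ₋₁), where T is noncentral t with n − 1 df and noncentrality d√n; the opposite tail is negligible. Miss rate = 1 − power.

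Example for control, n = 20, d = 0.5: critical value 2.093, noncentrality 0.5 × √20 = 2.236, power 56.4%, miss rate 43.6%. For VE, n = 40: critical value 2.023, noncentrality 3.162, power 86.9%, miss rate 13.1%.

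| True change (SD) | Missed, control n = 20 | Missed, VE n = 40 |
|---|---|---|
| 0.3 | 75% | 54% |
| 0.5 | 44% | 13% |
| 0.8 | 8% | 0.1% |

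If 20% of scan pairs were lost (a further assumption), the 0.5-SD miss rates would be 54% (n = 16) and 22% (n = 32).

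**4. Significant beside non-significant when the arms do not differ.** Take the same true 0.5-SD change in FE (n = 40) and control (n = 20), with independent arms:

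- FE significant, control not: 0.869 × 0.436 = 0.379, or 38%.
- Control significant, FE not: 0.564 × 0.131 = 0.074, or 7%.

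The imbalance comes from arm size alone and favours the hypothesised pattern. For FE against VE the arms are equal, so neither direction is favoured. The pattern of FE significant and VE not still occurs by chance in 0.869 × 0.131 = 0.114, or 11%, of trials with identical 0.5-SD changes.

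**The case against.** The strongest reply is that the Background sentence is a prediction and not a decision rule. Aim 3 is itself worded descriptively, and nowhere does the article say that p > 0.05 will be read as no change. That stands. A reader might infer that the investigators have committed themselves to this misreading; the text does not support so strong a statement. What it shows is a hypothesis that the named test cannot support.

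Second, between-group comparison is already contemplated. The Power analysis section speaks of differences between groups, and the Data analysis section promises treatment effects with 95% confidence intervals. This also stands in part, and it makes the fix easy. However, the ANCOVA is confined to motor and non-motor outcomes, and the MRI data section names its own test without a group term. A between-group contrast would in any case show a differential effect, not an absence of change.

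Third, the 44% is open to over-reading. It belongs to the control arm only, to an assumed 0.5 SD, and to an arm-wise test that the article does not spell out. For VE, the arm that matters most to the FE-versus-VE question, the figure under the same assumptions is 13%. All of this is accepted, which is why a range is given for both arms.

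Fourth, an equivalence margin for a mechanistic aim could be left to a fuller document. Agreed: the lack of a margin is not counted as a fault here. The mismatch between the stated hypothesis and the stated test lies within the article's own text.

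**Conclusion.** The point holds as a mismatch between hypothesis and test. As written, the plan can support the claim of differential brain effects only by placing a significant FE result beside non-significant VE and control results, or, if the test is pooled, not at all. This conclusion does not depend on any assumed effect size.

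The sizes are illustrative and rest on arm-wise paired tests at two-sided 0.05 without scan loss. Over 0.3 to 0.8 SD, a real change would be missed 75% to 8% of the time in control and 54% to 0.1% in VE. With equal true 0.5-SD changes, the hypothesised FE-versus-control pattern arises in 38% of trials, against 7% for its reverse.

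The importance is modest. The aim is mechanistic, and neither the primary UPDRS comparison nor the sample size depends on it.

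**What to change.** 1. In the Background, restate the Aim 3 hypothesis as a greater increase in activation and CBF from baseline to end of treatment in FE than in VE and than in control.
2. In the MRI data section, test this by a between-arm comparison of the change in supplemental motor area activation volume, adjusted for baseline and with Tukey's correction for three groups, and report each difference with its 95% confidence interval. This agrees with the between-group basis of the Power analysis section.
3. State that a non-significant within-arm test will not be reported as no change.

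A pre-stated equivalence margin is optional and is needed only if the investigators wish to claim absence of a relevant change in an arm. The article offers no basis for choosing one.

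The cost is a reworded hypothesis, one added model and one reporting rule, with no new data. The downside is a weaker permitted statement about the VE and control arms: the trial could say that FE changed more, but not that the others did not change.

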## Methods and design

### Study design

This single center, prospective, rater-blind, three arm clinical trial will investigate the efficacy of a FE paradigm on motor and non-motor symptoms in individuals with PD. A total of 100 individuals with mild to moderate idiopathic PD will be enrolled. CYCLE Trial protocol is approved by the Cleveland Clinic Institutional Review Board and all participants will sign an informed consent prior to beginning the study. Written informed consent was obtained for any photographs that have been taken for publication. A schematic overview of the enrollment, testing, and intervention is shown in Figure 1.

